### Planned data analysis strategy

For the actual survey, descriptive statistics will be calculated for each center as well as center-overlapping. Descriptive data of drop-outs and completers will be compared. For the primary outcome, a confirmatory hypothesis test will be performed with a two-sided significance level set to 5%. The analysis (Fisher’s exact test) will be based on an intention-to-treat population, which means that all clusters/participants are analyzed as randomized. Drop-out will conservatively be defined as non-compliant guideline adherence. However, we assume a minimal drop-out rate of ≤ 10%, as we examine care providers in two defined service regions. For secondary outcomes with continuous variables, linear mixed model will be applied with inclusion of data with missing values. If normal distribution assumption is violated, monotonous and continuous data transformation (logarithmic or inverse normal transformed (RIN, e.g., rankit)) or non-parametric tests (Mann-Whitney *U* test, Wilcoxon test)) will be used. The per-protocol population will be analyzed in a second step and will be defined as all participants with available T0 and T1 data for the primary outcome measure.

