### Data collection and management

During the examination statements and personal information of the participants is gathered and electronically stored. They will be stored in double pseudonomized form, no names or initials will be used but a code with numbers and letters. In the data table there will be no entry who filled in the data, when and from where the survey was filled in. The software LimeSurvey ® fulfills the German valid data protection standard and the complete process was approved by the responsible data protection officer of the LMU university hospital. The saved data will be stored according to national regulations in the archives of the Department of Psychiatry, Psychotherapy, and Psychosomatics of the University of Augsburg. The data is provided on a voluntary basis after giving consent. Participants are informed about the basis regulation of data protection (Art. 12 ff. DSGVO). Furthermore, they may withdraw their consent at any time.

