### Sample size justification and planned data analysis strategy

Sample size is based on the primary outcome. Our calculations are based on the results of the already conducted survey, which has shown only 40% orientating to the guideline in clinical practice [10]. We therefore conclude p1 = 0.4 of the participants in the control group will reach the cut-off regarding guideline compliance (≥ 30 points and five correctly answered cardinal questions). In the experimental group (MAGICapp), we expect p2 = 0.6, meaning that in this group, 50% more than in the control group will reach the cut-off to guideline compliance. Applying the two-sided Fisher’s test with *α* = 0.05, a power of 1-*β* = 0.8, and a distribution of N2/N1 = 1, it is calculated that 204 participants were required if no cluster randomization was applied [30]. In this cluster randomized trial, the design effect (DE) is needed to calculate the final sample size [31]. The DE is defined as DE = 1 + (*m* - 1) * *ICC*, with *m* being the average cluster size and *ICC* the intracluster correlation coefficient. We assume an average cluster size of 17 and an *ICC* of 0.01 [32] leading to correction factor of 1.164 (DE = 1 + (17 − 1) * 0.01). Consequently, the sample size is *N* = 204 * 1.16 = 237 participants, which means on average 237/14 = 16.93 per cluster.

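### The confirmatory Fisher's exact test ignores the 14 randomised clusters, so its 5% level holds only if the intracluster correlation stays near 0.01 and cluster sizes are nearly equal

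*Protocol article*

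**What the plan says.** The *Study design* and *Intervention* sections of the protocol article make the cluster the unit of randomisation: 17 clinics grouped into 14 clusters. Cluster randomisation was chosen because colleagues in one unit would talk to each other.

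The section *Sample size justification and planned data analysis strategy* accepts that participants within a cluster are correlated: "In this cluster randomized trial, the design effect (DE) is needed to calculate the final sample size". It takes an average cluster size of 17 and an ICC of 0.01.

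The section *Planned data analysis strategy* then says that for the primary outcome "a confirmatory hypothesis test will be performed with a two-sided significance level set to 5" per cent, and names the test: "The analysis (Fisher’s exact test) will be based on an intention-to-treat population". It mentions no cluster-level summary, random effect, GEE or robust variance for this test. A linear mixed model is named only for continuous secondary outcomes.

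**The concern.** Fisher's exact test gets its p-value from a null distribution in which every participant is an independent observation. The sample-size section assumes that they are not. The two sections therefore rest on incompatible assumptions about the same endpoint.

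Positive intracluster correlation makes the difference between arms more variable than the test allows for, so the true type I error exceeds what the test would have under independence. This is the trial's only confirmatory test, and the *Discussion* says the results will be used for the update of the schizophrenia guideline as a living guideline. A false finding of superiority would have a direct use.

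**Working it through.** **Inputs from the article.** "p1 = 0.4 of the participants in the control group"; "we expect p2 = 0.6"; "a power of 1-*β* = 0.8"; "a distribution of N2/N1 = 1"; two-sided α = 0.05; cluster size m = 17; ICC = 0.01; 14 clusters; 204 participants before and 237 after the design effect (DE).

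**Assumptions of mine.** Seven clusters per arm; beta-binomial outcomes; ICCs of 0.02, 0.05 and 0.10; uneven sizes of 5, 8, 10, 14, 17, 25 and 40 in each arm (total 119, coefficient of variation about 0.66).

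**1. Reproducing the plan's figures.** Full enumeration of the two-sided Fisher test at 0.4 against 0.6 gives power 0.794 with 101 per arm and 0.8008 with 102 per arm, so N = 204. The design effect is 1 + (17 − 1) × 0.01 = 1.16, and 204 × 1.16 = 236.6, so N = 237. Both figures are confirmed. (The text also prints the factor as 1.164; its formula gives 1.16, and 237 is unaffected.)

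**2. Why a larger N does not help the error rate.** With equal clusters, the variance of the difference in proportions is DE times its value under independence. An unadjusted z-test at 1.96 therefore has true size

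2 × [1 − Φ(1.96 / √DE)].

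N appears only through m. The number of clusters is fixed at 14, so added participants make clusters larger: 204/14 = 14.57 gives DE = 1 + 13.57 × 0.01 = 1.136, and 237/14 = 16.93 gives 1 + 15.93 × 0.01 = 1.159. The inflation raises DE slightly. It does not offset it.

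At ICC 0.01, √1.16 = 1.077 and 1.96/1.077 = 1.82, giving a size of 6.9%. At ICC 0.05, √1.80 = 1.342 and 1.96/1.342 = 1.46, giving 14.4%.

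**3. Size of the planned Fisher test.** Fisher's test is conservative, so it starts below 5% and part of the excess is absorbed. The table shows simulation results: 100,000 trials per scenario, 7 clusters of mean size 17 per arm (N = 238), common pass rate 0.4 under the null. The last two columns are for a t-test on cluster pass rates with 12 df and equal clusters.

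| ICC | DE | Unadjusted z-test, size | Fisher, equal clusters | Fisher, uneven clusters | Cluster t-test, size | Cluster t-test, power (0.4 v 0.6) |
|---|---|---|---|---|---|---|
| 0 | 1.00 | 5.0% | 4.0% | 3.9% | 5.0% | 0.82 |
| 0.01 (plan) | 1.16 | 6.9% | 5.4% | 6.3% | 5.0% | 0.76 |
| 0.02 | 1.32 | 8.8% | 7.1% | 8.7% | 4.9% | 0.70 |
| 0.05 | 1.80 | 14.4% | 12.1% | 16.1% | 5.1% | 0.57 |
| 0.10 | 2.60 | 22.4% | 19.8% | 26.0% | 5.1% | 0.43 |

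A separate simulation with equal clusters and rate 0.4 gave 5.1%, 7.7%, 12.8% and 20% for Fisher's test at ICC 0.01, 0.02, 0.05 and 0.10. With uneven clusters it gave about 7% and 17% at 0.01 and 0.05. The conclusions are therefore stated as ranges. At a common rate of 0.5 with equal clusters, Fisher's test has size 4.8% at ICC 0.01 and 11.5% at 0.05.

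**4. What the inflation does achieve.** With N = 238 and ICC 0.01, the unadjusted Fisher test rejects in 82% of trials at 0.4 against 0.6. Power is restored for that test; its level is not.

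**The case against.** The strongest defence is that, under the plan's own assumptions, almost nothing goes wrong. At ICC 0.01 with equal clusters the level is between 4.8% and 5.4%, because Fisher's conservatism offsets the clustering. This stands. A reader might infer that the primary p-value is badly wrong even on the plan's own figures, and the figures do not support that. The article gives one ICC and an average cluster size only, so the 7% to 26% entries rest on my assumptions. Balancing by hospital type was not simulated and could lower the inflation. Part of the programme (the Zoom presentation, the fortnightly expert board, the emails) goes to participants in both arms and is not specific to a clinic, so the mode of training does not itself prove a high ICC.

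Three further readings are tempting and are not supported:

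- *The plan reports a wrong confidence interval.* It specifies no interval for the primary outcome. One computed on the same independence basis would be too narrow, but that is a consequence and not a stated error.
- *The data cannot support a cluster analysis.* A reader might infer this from "In the data table there will be no entry who filled in the data, when and from where the survey was filled in". That sentence describes pseudonymisation and does not say that a coded cluster variable is absent. Descriptive statistics are planned by centre, and the *Randomization* section has the statistician blinded to how clinics and clusters match, which suggests masked codes.
- *The protocol is merely silent.* A statistical analysis plan is promised before the database closes, but the test is already named here. A later plan must either inherit it or contradict it.

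The wording about analysing clusters and participants as randomised does not rescue the test either. It defines the intention-to-treat population and is not an adjustment for clustering.

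**Conclusion.** The point holds. The article enlarges N for clustering and then fixes a confirmatory test that ignores it. At ICC 0.01 the true level is about 5% with equal clusters and about 6–7% with markedly uneven ones. For larger assumed ICCs, with equal clusters and a pass rate of 0.4, it is about 7–8%, 12–13% and 20% at 0.02, 0.05 and 0.10.

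The harm at the planned ICC is small. The case for change is that the 5% level then depends on one assumed ICC proving right and on nearly equal clusters. The second condition is doubtful, since the clusters range from small community hospitals to university hospitals and some combine two sites. A cluster-level t-test kept its level near 5–6% throughout and needs neither condition.

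**What to change.** Before database closure, replace Fisher's test as the confirmatory analysis with one prespecified method that respects the clusters:

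- a t-test on cluster pass rates with 14 − 2 = 12 df; or
- a mixed-effects logistic model or GEE with a small-sample correction suited to 14 clusters; or
- a permutation test over the cluster allocation that follows the balancing by hospital type.

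Keep Fisher's test as descriptive only. Base any interval for the primary outcome on the chosen method.

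**Cost.** Only the wording of the protocol and analysis plan changes, and no new data are needed. The price in precision should be stated openly. With about 237 participants, power of the cluster-level t-test is about 0.76 at ICC 0.01, against the stated 0.80, and about 0.57–0.59 at an assumed ICC of 0.05. Relative to an interval computed as if participants were independent, the width grows by √DE × 2.179/1.960, where 2.179 is the 97.5% point of t with 12 df. That is 1.077 × 1.112 = 1.20 at ICC 0.01 and 1.342 × 1.112 = 1.49 at ICC 0.05. The power statement should be revised to match the chosen analysis.

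### The optional Mann-Whitney/Wilcoxon analysis of continuous secondary outcomes ignores the clusters; a nominal 5% test runs at about 7% at the protocol's ICC of 0.01, and higher if the ICC is larger

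*Protocol article*

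**What the plan says.** The section Planned data analysis strategy of the protocol article sets the main secondary analysis: "For secondary outcomes with continuous variables, linear mixed model will be applied with inclusion of data with missing values". It names no random effects or covariates.

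The next sentence gives the fallback. It begins "If normal distribution assumption is violated, monotonous and continuous data transformation" and lists the logarithm and the rank-based inverse normal transform (rankit) as examples. After an 'or', it offers the Mann-Whitney U test and the Wilcoxon test. No clustered version of either test is mentioned. Nor is it said whether they would be applied to T1 values, to changes, or to T0-T1 pairs.

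The sample size section takes a different view of clustering: "In this cluster randomized trial, the design effect (DE) is needed to calculate the final sample size". Its inputs are given as "We assume an average cluster size of 17 and an *ICC* of 0.01". The section Study design states that 17 clinics form 14 clusters, and that clusters were chosen because colleagues in one unit would talk to each other.

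**The concern.** The standard Mann-Whitney and Wilcoxon tests take every participant as an independent observation. Here the randomized unit is the cluster, and the protocol itself expects correlation within clusters and inflates its sample size for it. A test that ignores this correlation understates the variance of the arm comparison and rejects a true null hypothesis too often.

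This is more than an unstated detail, because the article names specific tests. The branch covers the scales for digital health expertise and shared decision making, which the Abstract and Study objectives list among the aims on which superiority is to be shown. A false positive there would support a claim that the trial sets out to make.

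The word Wilcoxon adds a second problem. As the rank-sum test it duplicates Mann-Whitney. As the signed-rank test it compares T0 with T1 within an arm and says nothing about the difference between arms.

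**Working it through.** **Inputs from the article.** Mean cluster size m = 17, ICC = 0.01, 14 clusters, N = 237. The two-sided 5% level is stated for the primary test and assumed here for the secondary tests.

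**Assumed inputs.** Seven clusters per arm; ICCs of 0.02, 0.05 and 0.10 as a range, because the article gives an ICC only in the sample size for the binary primary outcome; and a set of unequal cluster sizes from 6 to 40 that sum to 238.

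**Step 1: reproduce the protocol's own figures.** With "We therefore conclude p1 = 0.4 of the participants in the control group" and "we expect p2 = 0.6", exact power of the two-sided Fisher test is 0.7939 with 101 per arm and 0.8008 with 102, so 2 × 102 = 204 is confirmed. DE = 1 + (17 − 1) × 0.01 = 1.16. Then 204 × 1.16 = 236.64, rounded up to 237, and 237/14 = 16.93. (The printed factor of 1.164 does not follow from the formula; the final N does follow from 1.16.)

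**Step 2: approximate type I error of a rank test that ignores clusters.** Clustering inflates the variance of the test statistic by about DE, so

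true α ≈ 2 × [1 − Φ(1.96/√DE)].

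At ICC 0.01: √1.16 = 1.077, 1.96/1.077 = 1.820, giving α ≈ 0.069.

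**Step 3: check by simulation.** 14 clusters, 7 against 7, 238 participants, a skewed (log-normal) outcome, no true effect, 4,000 runs per setting. The Monte Carlo standard error near 0.07 is √(0.07 × 0.93/4000) = 0.004.

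| ICC | DE | Formula | Simulated, equal clusters | Simulated, unequal clusters |
|---|---|---|---|---|
| 0 (assumed) | 1.00 | 0.050 | 0.047 | 0.052 |
| 0.01 (protocol) | 1.16 | 0.069 | 0.068 | 0.072 |
| 0.02 (assumed) | 1.32 | 0.088 | 0.084 | 0.098 |
| 0.05 (assumed) | 1.80 | 0.144 | 0.148 | 0.171 |
| 0.10 (assumed) | 2.60 | 0.224 | 0.216 | 0.261 |

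With ICC 0 the test holds its level, so the excess comes from clustering. A separate simulation with normal outcomes, with equal cluster sizes and with a coefficient of variation of 0.6, gave 0.070/0.073, 0.137/0.172 and 0.217/0.258 at ICC 0.01, 0.05 and 0.10.

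**Step 4: does using T0 help?** Mann-Whitney on T1 − T0 changes gave 0.067-0.074 at ICC 0.01 and 0.142-0.144 at ICC 0.05, so the inflation remains. In this simulation the changes carry the same ICC as the raw scores; if cluster differences are more stable over time than that, the excess would be smaller. T0 matters for power: at ICC 0.01 and an assumed effect of 0.35 SD, power on T1 alone against changes was 0.73 and 0.90 at a T0-T1 correlation of 0.7, but 0.74 and 0.74 at 0.5. All four figures belong to tests with inflated α.

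**Step 5: does respecting the clusters cure it?** A t test on the 14 cluster mean ranks held type I error at 0.044-0.058 over ICC 0 to 0.10, with equal or unequal sizes. Cluster means of T0-adjusted ranks gave 0.049-0.055 at ICC 0.01 and 0.05.

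**The case against.** The strongest reply is that this is one optional branch for outcomes that are not confirmatory. Only the primary test is described in such terms: "a confirmatory hypothesis test will be performed with a two-sided significance level set to 5" per cent. At the only ICC in the article the excess is about two percentage points, and the larger figures rest on ICCs that the article does not state. All of this is correct. It limits the weight of the point but does not make the named tests valid.

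Several stronger readings are tempting and are not supported:

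- A reader might infer that every failed normality check leads to an invalid test. Transformation is listed first and can stay within the mixed model; only the second option is at fault. How often it would be used cannot be judged, because the article reports no distributions for these scales.
- A reader might blame the loss of the T0 value for the wrong error rates. Under randomization, omitting a baseline costs power and does not raise type I error. Loss of T0 is not established either, since Mann-Whitney can be applied to changes.
- A reader might say that the fallback throws away clusters and T0 that the mixed model contained. The article does not list the terms of that model.
- A reader might object that the choice between transformation and rank test is left until the data are seen. The Randomization section promises a statistical analysis plan before the database closes and a blinded analysis. The selection rule and the model terms commonly belong in that plan, which is not at hand.

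**Conclusion.** The point holds for the Mann-Whitney/Wilcoxon option alone. Followed as written, it gives a true type I error of about 7% instead of 5% at the protocol's ICC of 0.01 and mean cluster size of 17. If the questionnaire scales cluster more strongly, it gives about 14-17% at an assumed ICC of 0.05 and 22-26% at 0.10. These figures rest on 7 clusters per arm and a two-sided 5% level; unequal cluster sizes account for most of the upper ends. Under the signed-rank reading of Wilcoxon, the question of superiority is not tested at all.

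The weight is minor to moderate: the rule is wrong as stated and should be changed, but it concerns secondary outcomes and a branch that may never be used.

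**What to change.** Delete the unadjusted Mann-Whitney and Wilcoxon tests. When normality fails, use the rank-based inverse normal transform that the protocol already permits, in a mixed model with a random cluster intercept, the T0 value as covariate and small-sample degrees of freedom suited to 14 clusters. Alternatively, prespecify a cluster-level permutation test that follows the balancing used in the randomization. The checks above used cluster-level t tests on ranks; the mixed model itself was not simulated.

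The cost is a change of wording, a little more analysis work and somewhat wider intervals. With the effect of 0.35 SD assumed above, cluster means of T0-adjusted ranks had power 0.75 at ICC 0.01 and a T0-T1 correlation of 0.5, against 0.74 for the unadjusted test on T1. At ICC 0.05 and the same correlation, power was 0.56 against 0.70, but the second figure comes from a test whose true level there was about 13%. The analysis file must carry a cluster code. A neutral code is enough, so the planned blinding of the statistician is kept.

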### Trial status

The current protocol version is 1.3 (12.02.2022). The date of first enrolment was 16 May 2022 and is completed due to the design of the study as a cluster-randomized trial. The estimated date of the end of data recruitment will be 30. November 2022.

### Ancillary and post-trial care

There is no anticipated harm and compensation for trial participation. Within all participants, 50 specialist books are raffled as compensation of the time spent for the study.

### Dissemination

The results of this protocol study will be published in peer-reviewed journals and presented at national and international conferences. All project partners agreed on a publication and authorship agreement, which regulated the procedure for publications in detail.

## Discussion

The purpose of guidelines is to translate research and its results into clinical practice and support clinicians in their everyday decisions. However, the implementation of guidelines in clinical practice is despite long years of implantation research insufficient up to date. This gap keeps persisting if implementation is not regarded in a given context—the success of complex interventions is based on an integration of both implementation and context [33]. The process of integration is described by the ‘Context and Implementation of Complex Interventions (CICI) framework’ [33]. This framework comprises three with one another connected dimensions—context (seven domains—geographical, legal, political, epidemiological, socio-cultural, socio-economic, ethical context), implementation (five domains—implementation theory, process, strategies, agents and outcomes), and setting. The setting is the physical location, in which the intervention and its implementation interact with the context.

A variety of different implementation strategies exist [6, 7]. There is probably no superior strategy fitting to all situations [4, 11, 34]. Moreover, insufficient guideline adherence indicates that no implementation strategy has sustainably succeeded so far. Consent has been reached that guideline implementation can be achieved (1) through multifaceted intervention strategies [7, 8, 35–37], (2) the identification of barriers and facilitators [12, 34], and (3) an involvement of the guideline users in the guideline development process [12, 35].

The multifaceted strategy of the SISYPHOS project includes different aspects of the CICI framework and aims at closing the gap between research and practice as well as leading to a behavioral change concerning guideline adherence. The results of the cluster-randomized study will be used for the update of the German schizophrenia guideline as the worldwide first living schizophrenia guideline. This trial is the first trial evaluating the efficacy of a guideline implementation with the evidence ecosystem MAGICapp following the idea to overcome the evidence-practice gap [4]. However, one meta-analysis indicates that classical implementation strategies of non-living guidelines, such as distribution of educational material, educational meetings, reminders, or feedback, have limited impact of the provider performance [4]. In that regard, it has to be investigated whether novel guideline formats (e.g., living guidelines) presented in an evidence ecosystem have an added value in provider performance—this concept will be investigated in our trial. A schizophrenia living guideline will make current evidence-based knowledge for treatment of patients with schizophrenia anytime available. In this context, a sustainable implementation of the guideline for schizophrenia in a living guideline format could be achieved. In summary, until now, it remains elusive whether living guideline systems are superior in terms of the user’s knowledge gain. This question will be answered with the planned trial.

